#### Tertiary outcome

In addition to answering how the postoperative volumes of a primarily surgical relieved CSDH can be influenced by the administration of TXT compared to embolization of the MMA and how high the re-operation rate per treatment arm is, the aim is to show which constellation of symptoms lead to the indication for revision-operation in each case. For this purpose, the hematoma volumes imaged at the follow-up periods will be correlated with the neurological deficits recorded at the follow-up times according to the NIHSS score. Furthermore, the neurological outcome at the end of the study at the 3-month follow-up will be assessed using the modified Rankin Scale and the NIHSS, the results will be compared with the baseline values before surgical hematoma relief.

The National Institutes of Health Stroke Scale (NIHSS) is a scoring system from the field of neurology and was originally used for the early detection and monitoring of stoke progression. The NIHSS score covers the following areas: Level of consciousness, eye movements, integrity of visual fields, facial movements, arm and leg muscle strength, sensation, coordination, speech, language and neglect. Each impairment is rated on an ordinal scale of 0 to 2, 0 to 3, or 0 to 4. The scores are summed up to give a total score of 0 to 42 (the higher the score, the more severe the neurological deficit) [9]. In addition to the diagnosis and follow-up of ischemic strokes, the NIHSS represents an evaluation of the core symptoms of a chronic subdural hematoma that is accepted in the current literature, both in the context of acute diagnosis and in the follow-up situation.

The modified Rankin Scale measures the degree of disability or dependence in the daily activities of people who have suffered a stroke or other causes of neurological disability. The following scaling is used [26].0: No symptoms.1: No relevant impairment. Can carry out everyday activities without restriction despite minor neurological deficits.2: Slight impairment. Can take care of themselves without help but is restricted in everyday life.3: Moderately severe impairment. Needs help in everyday life but can walk without assistance or with aids (walking stick, rollator).4: Severe impairments. Needs help with personal hygiene, cannot walk without assistance.5: Severe disabilities. Bedridden, incontinent, requires constant nursing assistance.

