## Assignment of interventions: allocation

### Sequence generation {16a}, concealment mechanism {16b}, and implementation {16c}

After the neurosurgeon has checked the inclusion and exclusion criteria, the participants are assigned to treatment with tranexamic acid or embolization in a 1:1 ratio in each study center by means of block randomization after they have given their informed consent and the baseline data have been recorded.

If, in the course of the randomized group allocation, it will be apparent that there are exclusion criteria for inclusion in the test group in the sense of contraindications for the administration of tranexamic acid, or if it will be determine during the procedure that vascular anomalies prevent embolization in patients randomized to the control group, a crossover to the corresponding comparison group is possible after prior further clarification.

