## Data collection and management

### Plans for assessment and collection of outcomes {18a} and data management {19}

Neurological examination results (NIHSS and mRS) at baseline and at each follow-up time point will be recorded and securely stored by the clinical investigators and supporting study personnel in the form of paper data sheets. The size and extent of the CSDH will be measured using CT or MRI scans without contrast. The volume is measured using a medical image viewing program. (Fig. 2) Follow-up is carried out as shown in Table 1 at 1 week, 1, 2, and 3 months postoperatively after relief of the CSDH during outpatient follow-up visits.

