**Fig. 2 Fig2:**
[figure not shown]
Preoperative volume measurement of a right-sided hemispheric chronic subdural hematoma using the CT data set

The following intervention-associated complications will be documented as part of the study:Vascular dissections caused by the guidewireDislocation of embolized materialIschemia caused by vascular occlusion during the interventionInflammation or abscesses at the puncture siteVascular fistula in the area of the puncture siteRetinal blindnessEpidural hematomas after perforation of the meningeal arteryAllergic reactions to the contrast mediumAcute renal failure

The following complications or adverse events associated with the use of tranexamic acid will be documented:Intolerance reactionsPulmonary embolismsVenous thrombosisEpileptic seizuresMyocardial infarctionsCerebral ischemic infarctionsAcute renal failure

All research data, including baseline data (NIHSS, mRS, hematoma volume, patient demographics and characteristics) prior to surgery, will be collected anonymously in an electronic data collection form at each study center. The PI of the trial summarizes these for all centers and exports data for statistical analysis. All investigators will be trained to perform outcome measurements and will be introduced to the data management prior to recruitment of the first patient.

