## Statistical methods

### Statistical methods for primary and secondary outcomes {20a}

The baseline data and outcome parameters are subjected to a simple descriptive data analysis (median, minimum, maximum and standard deviation in each case; mean only for metrically scaled characteristics).

For difference tests for nominal variables (gender, use of anticoagulation prior to surgery, occurrence of complications due to adjuvant therapy procedures, need for revision surgery), the Pearson chi-squared test is used.

For difference tests of ordinally scaled measured variables (NIHSS, mRS) within the respective groups at different points in time (linked samples), the data collected is tested for normal distribution using the Shapiro–Wilk test. In the case of a parametric distribution, the *t*-test is used for linked samples. In the case of a non-parametric distribution, the Wilcoxon test is used for connected samples (for two-group tests).

For the bivariate dependency analysis of the ordinal scaled characteristics between the two groups at the same point in time, the *t*-test for unconnected samples is used for a parametric distribution and the Mann–Whitney *U*-test for a non-parametric distribution after applying the Shapiro–Wilk test.

For metric variables (hematoma volume), which are subject to a normal distribution, the *t*-test for dependent samples is used to analyze the respective groups at different points in time. In the case of a non-parametric distribution, the Wilcox sign-rank test is used for the analysis.

For the bivariate dependency analysis of the metric characteristics between the two groups at the same point in time, after applying the Shapiro–Wilk test, the *t*-test for unrelated samples is used for a parametric distribution and the Mann–Whitney *U*-test for a non-parametric distribution.

In addition, a logistic regression is tested with the revision rate as the dependent variable and the treatment groups and baseline data as independent variables.

Furthermore, a correlation analysis of the relationship between the postoperative volume size and the revision rate as well as the postoperative neurological assessment and the revision rate is performed, in each case for mixed scaling pairs with the chi-squared test. The respective singular correlation analysis is followed by an analysis of the existence of a partial correlation between the two parameters in relation to the revision rate.

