### Trial status

This manuscript is based on trial protocol version 2.1, dated 25 April 2024. Recruitment at the leading center started on 01 May 2024. The patient recruitment has also started at a second study center. A further participating study center has recently been acquired. Recruitment has not started here. Several other potential study sites have been contacted. The end of the recruitment phase depends on the total number of participating study centers and is scheduled for the beginning of 2026 if a total of 5–8 sites are involved.

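### NIHSS and mRS are compared between arms without the baseline scores the trial collects: valid on average, but precision is given up that adjustment would recover at no cost

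*Protocol article*

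**What the plan says.** All references are to the protocol article.

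- **Between-arm test.** Statistical methods {20a} sets the comparison of ordinal scores as follows: "For the bivariate dependency analysis of the ordinal scaled characteristics between the two groups at the same point in time". A Shapiro–Wilk test decides between an unpaired t-test and a Mann–Whitney U-test. Neither has a place for a covariate.
- **Use of baseline.** The tertiary outcome section says of the 3-month mRS and NIHSS that "the results will be compared with the baseline values before surgical hematoma relief". The statistical section carries this out only inside each arm: "For difference tests of ordinally scaled measured variables (NIHSS, mRS) within the respective groups at different points in time (linked samples"), by paired t-test or Wilcoxon test.
- **Data available.** The section on outcome collection and data management {18a, 19} states: "Neurological examination results (NIHSS and mRS) at baseline and at each follow-up time point will be recorded". After the Fig. 2 legend, the list of research data reads "including baseline data (NIHSS, mRS, hematoma volume, patient demographics and characteristics) prior to surgery". The baseline scores therefore precede randomization.
- **Allocation.** Patients are assigned "in a 1:1 ratio in each study center by means of block randomization". The trial status section speaks of the recruitment timetable "if a total of 5–8 sites are involved".
- **The one adjusted model.** A logistic regression on treatment group and baseline data is planned, with revision surgery as its outcome. It does not cover NIHSS or mRS.

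**The concern.** A patient's deficit at presentation may well predict the deficit at 3 months. If so, a two-sample test that ignores it leaves explainable variation in the error term. It also cannot separate a treatment difference from a chance difference in presenting severity. The paired tests do not fill the gap. Every patient has just had the hematoma relieved, so both arms may improve whatever the adjuvant does, and two within-arm p-values say nothing direct about the difference between arms. No planned analysis of the neurological outcome uses arm and baseline together. At stake is the sharpness of the answer to a stated tertiary objective, from data that will be in hand anyway.

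**Working it through.** **1. Inputs.** From the sample size section: 138 per arm, alpha 0.05, power above 0.8, recurrence 10% against 2%. The following are not in the documents and are assumed: rho, the correlation of baseline with 3-month score, from 0.3 to 0.6; and the between-centre share of variance (ICC), from 0.02 to 0.10.

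**2. The plan's own figure.** Two-sided pooled z-test, no continuity correction, mean proportion 0.06:

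n = [1.96·√(2·0.06·0.94) + 0.842·√(0.10·0.90 + 0.02·0.98)]² / 0.08² = (0.658 + 0.279)² / 0.0064 ≈ 137.2, so 138 per arm and 276 in total.

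Power at 138 per arm is 80.2%. The figure reproduces. It rests on recurrence, so nothing below alters it.

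**3. Reference effect for a score.** The plan names no target difference for NIHSS or mRS. The difference that the unadjusted test detects with 80% power is used as a yardstick:

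d = (1.96 + 0.842)·√(2/138) = 0.337 SD.

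**4. Adjusting for baseline.** Residual variance falls by the factor 1 − rho². Power = Φ(d·√69 / √(1 − rho²) − 1.96), with d·√69 = 2.80. The equivalent unadjusted size per arm is 138/(1 − rho²).

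| rho (assumed) | Variance factor | Power | Equivalent n per arm |
|---|---|---|---|
| 0 | 1.00 | 80.0% | 138 |
| 0.3 | 0.91 | 83.6% | 152 |
| 0.4 | 0.84 | 86.4% | 164 |
| 0.5 | 0.75 | 89.9% | 184 |
| 0.6 | 0.64 | 93.8% | 216 |

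**5. Chance imbalance.** The baseline difference between arms has standard error √(2/138) = 0.120 SD. The unadjusted contrast takes up rho times the realized imbalance.

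- A typical imbalance (median absolute value 0.674 × 0.120 = 0.081 SD) shifts it by about 0.04 SD at rho 0.5.
- An imbalance of 1.96 standard errors (0.236 SD) shifts it by 0.071 SD at rho 0.3 and 0.118 SD at rho 0.5. Given that imbalance, the type I error is about 8% and 13%.
- Over all randomizations it stays at 5%.

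**6. Centre.** Adjusting for centre alone gives power of 80.8%, 82.0% and 84.0% at ICC 0.02, 0.05 and 0.10. Ignoring centre after blocking within it makes the test slightly conservative, with an actual alpha of about 0.048, 0.044 and 0.039.

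**The case against.** The strongest reply is that this is a preference about efficiency and not an error. Randomization makes the unadjusted test valid. The scales are tertiary, and the sample size does not depend on them. Surgery comes between the baseline score and randomization and is meant to relieve the deficit that was scored, so rho may be low; at 0.3 the gain is under 4 points. The 0.337 SD difference is a yardstick that the plan does not name. The power figures come from a linear model, which only approximates an ordinal analysis, particularly for NIHSS with its 0 to 42 range. An adjusted common odds ratio also answers a conditional question and is not the same quantity as the unadjusted one. All of this stands, and it limits the weight of the point.

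It does not remove the point. The tests are named in the text, so this is a stated choice and not a detail left to an unseen analysis plan.

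Four stronger readings are tempting, and the documents support none of them:

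- **That the planned test is biased or has an inflated error rate.** It does not, on average; the excess arises only conditionally on an imbalance.
- **That an imbalance carries over in full.** Only about rho times it does.
- **That leaving out centre matters as much as leaving out baseline.** The figures above show a small loss, in the conservative direction.
- **That the plan offers the within-arm tests as its treatment comparison.** It does not; a separate between-arm test is stated.

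**Conclusion.** The point holds as a free improvement. The planned comparison of NIHSS and mRS is sound on average but less precise than the collected data allow, and it is open to part of any chance difference in baseline severity. Over the assumed range of rho, 80% power becomes roughly 84% to 94% with baseline in the model. That range rests on three things: a correlation the documents do not give, a normal linear approximation, and a reference difference set to give 80% power. Nearly all of the gain comes from baseline; centre belongs in the model chiefly because allocation was blocked within it. The sample size and the comparison of revision rates are unaffected.

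**What to change.** In Statistical methods {20a}, replace the unadjusted between-arm tests of the two scales at 3 months with one pre-set model per scale:

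- **mRS:** proportional-odds regression on randomized arm, baseline mRS and centre, reporting the common odds ratio (conditional on the covariates) with its 95% CI.
- **NIHSS:** ANCOVA or an ordinal or rank-based model, with the choice fixed in advance, on randomized arm, baseline NIHSS and centre, reporting the effect estimate with its 95% CI.
- **Centre:** state one rule for small centres, for example pooling them below a named size, and use it in both models.
- **Within-arm pre-post tests:** keep as description only.

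The trial is open-label and recruiting, so the wording should be settled before outcome data are analysed; the choice of covariates then cannot be questioned later. The cost is a change of analysis text. No additional patients, visits or measurements are needed.

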### Objectives {7}

#### Primary objective

The primary aim of this study is to investigate how the postoperative volume decrease of a primarily surgically relieved CSDH can be influenced quantitatively and regarding to the time course by a postoperative adjuvant drug therapy with tranexamic acid in comparison to a postoperative interventional embolization of the MMA on the affected side in a study period of 3 months postoperatively.

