### Outcomes {12}

#### Primary outcome

The primary element to be investigated in this study is the postoperative volume development of a primarily surgically relieved unilateral CSDH over the course of 3 months postoperatively. For diagnostic purposes and documentation, cranial cross-sectional imaging using native cMRI or CT-scan and subsequent volumetry to visualize the residual hematoma volume in milliliters will be performed at the planned follow-up time points, 1 day postoperatively, 1 week postoperatively, 1 month postoperatively, 2 months postoperatively and 3 months postoperatively. The volumetry will be performed by a radiologist who is not involved in the study. Although he is not informed about the group assignment of each patient, he is not blinded because the group assignment can easily be identified from the radiological evidence of the embolism material in the imaging. All findings are considered in relation to each other and in relation to the initial findings before the operation. The planned examination intervals correspond to the current standard of care for postoperative imaging follow-up after CSDH surgery and reflect the procedure used in comparable studies [27].

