The significance level is set at *p* < 0.05 in each case.

The statistical analysis is performed with SPSS.

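### Hematoma volume is tested over time only within each arm and between arms only visit by visit, so no named test compares the volume course between tranexamic acid and embolization

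*Protocol article*

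**What the plan says.** The Primary objective asks how the postoperative volume decrease is influenced "quantitatively and regarding to the time course by a postoperative adjuvant drug therapy with tranexamic acid in comparison to a postoperative interventional embolization". That is a between-arm question with two parts, the amount and the course. The Primary outcome is "the postoperative volume development of a primarily surgically relieved unilateral CSDH over the course of 3 months postoperatively", measured at "1 day postoperatively, 1 week postoperatively, 1 month postoperatively, 2 months postoperatively and 3 months postoperatively". The same section adds: "All findings are considered in relation to each other and in relation to the initial findings before the operation".

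The section Statistical methods for primary and secondary outcomes {20a} gives hematoma volume two kinds of test:

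- **Within arm, across time.** The paired t-test "for dependent samples is used to analyze the respective groups at different points in time", or a Wilcoxon signed-rank test if the data are not normal.
- **Between arms, at one time.** "For the bivariate dependency analysis of the metric characteristics between the two groups at the same point in time", an unpaired t-test or a Mann-Whitney test.

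The only regression named is logistic, with revision as the outcome. On the error rate: "The significance level is set at" p < 0.05 for each test.

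**The concern.** For the time-course part of the objective, the relevant null is that both arms follow the same course. The one method the article assigns to volume across time has a different null: volume in this arm does not change. Patients are enrolled after evacuation, and neither arm goes without adjuvant treatment. A fall within an arm therefore mixes any adjuvant effect with natural resorption. If it is measured from the preoperative scan, it also includes the operation itself, which precedes randomization.

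At stake is how the primary outcome is read. Two significant falls could be taken as support for the stated equivalence aim. One significant and one non-significant fall could be taken as a difference in speed. Neither pattern is evidence on the arm difference.

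**Working it through.** **Inputs from the article.** 138 patients per arm, alpha 0.05, and five postoperative scans plus a preoperative volume. It gives no volume mean, SD or correlation, so everything below is either expressed in standardized change or labelled as assumed. Complete follow-up is assumed.

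**The plan's own figure.** For 10% against 2% recurrence, two-sided alpha 0.05 and 80% power, with pooled variance:

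n = [1.96·√(2·0.06·0.94) + 0.8416·√(0.10·0.90 + 0.02·0.98)]² / 0.08² = 137.2, so 138 per arm and 276 in total, with power 0.802. The figure reproduces. It comes from recurrence and not from volume, so this point does not alter it.

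**Step 1: within-arm tests when both arms share the same true change.** Let d be the mean change divided by the SD of the change. Power p per arm comes from the noncentral t distribution with 137 degrees of freedom and noncentrality d·√138. The arms are independent, so the chance that exactly one is significant is 2p(1−p).

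| d | p per arm | exactly one arm significant |
|---|---|---|
| 0 | 0.050 | 9.5% |
| 0.10 | 0.215 | 34% |
| 0.167 | 0.495 | 50% (the maximum) |
| 0.20 | 0.645 | 46% |
| 0.24 | 0.799 | 32% |
| 0.30 | 0.938 | 12% |
| 0.50 | >0.999 | about 0 |

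The two patterns belong to different situations. Large falls make both arms significant. Small to moderate falls make them disagree.

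**Step 2: simulation with identical courses.** Assumptions: 3,000 trials per scenario, five visits, SD 30 mL, AR(1) correlation 0.6 and 0.8, and paired tests of each later visit against day 1.

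- Steep common fall (60 to 15 mL): both arms are significant at month 3 in 100% of trials.
- Moderate fall (60 to 46 mL): at least one of the four visits is discordant in 60% to 69%.
- Shallow fall (60 to 55.5 mL): at least one visit is discordant in 57% to 66%.
- No change at all: at least one visit is discordant in 25% to 26%. This is the fair benchmark for the two lines above.

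**Step 3: the planned between-arm tests, same simulation.** At month 3 they reject in 4.4% to 5.7% of trials, which is nominal. At least one of the five visits rejects in 14.5% to 19% (1 − 0.95⁵ = 22.6% if the visits were independent).

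**Step 4: which between-arm analysis would serve.** A between-arm test of the day-1 to month-3 change also holds its level (4.6% to 5.7%), but it can be inefficient. With an assumed true arm difference, an unadjusted raw change score had 25% to 60% power, against 80% to 85% for the planned Mann-Whitney test at month 3. A single-visit analysis of covariance on log volume held about 5% under the null. It matched or exceeded the planned month-3 test at every correlation tried.

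**The case against.** The strongest reply is that between-arm comparisons of volume are planned at every visit. Under randomization, arms with the same course have the same expected volumes throughout, and arms whose courses diverge will differ at some visit. The per-visit series therefore does show when the arms separate. This stands. It would be wrong to infer that the time-course question can be answered only by setting two within-arm p-values side by side, or that the planned between-arm tests reject too often when the courses are the same. Each holds about 5%.

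A reader might also take the 12% to 50% discordance as a false-positive rate to be set against 5%. It is not one. No planned test rejects on discordance, two independent tests disagree 9.5% of the time when nothing changes, and rejecting no change when volume has truly fallen is correct. Nor does the article say that within-arm p-values will be compared between arms. That misuse is a risk and not a stated plan.

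Finally, change from an initial scan could itself count as a metric characteristic compared between groups, and a statistical analysis plan that is not shown may hold a longitudinal model. Both are possible. But the methods section names hematoma volume as the metric variable, ties the between-arm test to a single time point, and assigns the paired test to the time dimension. The point rests on that stated choice and not on an omission.

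**Conclusion.** The point holds in a limited form. The amount of residual volume at each visit has a valid between-arm test. The course has none: separate visit-wise tests at p < 0.05 do not test whether the courses differ, give no single answer, and make no use of the baseline volume already collected. The within-arm tests carry no information on the arm difference. With 138 per arm they would be expected to be significant in both arms after surgical relief (power over 99.9% at 0.5 SD). For identical changes of 0.1 to 0.3 SD they split in about 12% to 50% of trials.

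The analytic figures depend only on the sample size and the standardized change. The simulated figures rest on assumed volumes, SDs and correlations. This concerns the primary outcome and is cheap to correct, but it does not invalidate the planned visit-wise comparisons.

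**What to change.** In Statistical methods for primary and secondary outcomes {20a}:

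1. Report within-arm volume change descriptively, with 95% confidence intervals and no p-values. State that no conclusion about the effect of either treatment, or the difference between them, rests on within-arm p-values.
2. Name one between-arm analysis for the primary objective: a repeated-measures mixed model of postoperative volume with arm, visit and arm-by-visit terms, adjusted for baseline volume. Say whether baseline is the day-1 or the preoperative volume.
3. Name one primary contrast, for example the adjusted arm difference at 3 months, and use the arm-by-visit term for the time course.
4. Do not substitute an unadjusted raw change score, which can lose power against the planned month-3 test.
5. If volume is log-transformed, state how 0 mL is handled, for example log(volume + constant) with the constant given.

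**Cost.** No extra patients or scans, and the model can be fitted in SPSS. The downsides are giving up the within-arm p-values and some additional model specification.

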### Sample size {14}

In order to estimate the required sample size, the volume change of a primary operated CSDH under the adjuvant therapy forms to be investigated is analogized with the recurrence rates of primary operated and adjuvant embolized or adjuvant drug-treated CSDH in the literature with regard to the target value defined within the primary objective. For example, the MEMBRANE study, which is currently being recruited, assumes a recurrence rate of 10% when combined surgical and interventional therapy is used [11]. In comparison, the work of Hibahashi et al. [27] puts the recurrence rate of CSDH treated with a combination of surgery and medication at around 2%. Based on this, using the *z*-test for independent samples and an error of the first kind (*α* = 0.05), a sample size of 276 patients (138 per group) is required to achieve a power > 0.8 to detect a difference of 8%.

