### Methods in analysis to handle protocol nonadherence and any statistical methods to handle missing data {20c}

Missing data will be avoided as much as possible by planning scheduled visits well in advance. If a significant amount of data is missing for any of the primary endpoints or other analyses, we will conduct exploratory analyses to assess the impact of the missing data, according to the EMA-guidelines [4]. Depending on the amount of missing data, it will be assessed whether missing covariates can be replaced by multiple imputation with predictive mean adjustment.

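### The primary volume outcome is tested separately at every visit at an unadjusted 0.05, with no primary visit or single contrast named

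*Protocol article*

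**What the plan says.** The Primary outcome section defines the primary element as the development of residual volume over 3 months, and says that "subsequent volumetry to visualize the residual hematoma volume in milliliters will be performed at the planned follow-up time points". It lists five postoperative scans: day 1, week 1, and months 1, 2 and 3. The Primary objective adds that both the amount of volume decrease and its time course are of interest. Neither section picks out one visit or one summary measure.

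The analysis is in Statistical methods for primary and secondary outcomes {20a}, which names hematoma volume as the metric variable. The between-arm rule begins "For the bivariate dependency analysis of the metric characteristics between the two groups at the same point in time". It then lets a Shapiro–Wilk test decide between the unpaired t-test and the Mann–Whitney test. Within-arm comparisons between time points are also planned. The section closes with the level for all of these tests: "The significance level is set at *p* < 0.05 in each case".

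The only other significance level is in Sample size {14}: "error of the first kind (*α* = 0.05", attached to a single comparison of recurrence rates.

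**The concern.** A confirmatory trial needs one rule that turns its data into an answer to the primary question. Here the arms can be compared four or five times on the primary outcome, each time at 0.05, and no rule says which comparison decides. If month 1 is significant and month 3 is not, the article cannot say what the trial found, and either result could be presented as primary.

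The trial is open label and is already recruiting, so choosing the deciding visit after seeing results by arm is a practical risk. This is more than detail left for a later analysis plan: {20a} positively prescribes separate tests and gives each one the full 0.05.

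**Working it through.** **Inputs from the article**
- Five postoperative scans, four of them after day 1 (Primary outcome).
- A separate between-arm test at each time point, each at 0.05 ({20a}).
- 138 patients per arm, 1:1 allocation (Sample size {14}, Trial design {8}).

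**Input assumed**
- The between-visit correlation r of volumes within a patient. The article gives none, so 0.5 to 0.9 is shown, with independence as the upper case.

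**Step 1: the article's own figure.** Sample size {14} takes 10% for surgery plus embolization ("assumes a recurrence rate of 10% when combined surgical and interventional therapy is used") and about 2% for surgery plus medication ("puts the recurrence rate of CSDH treated with a combination of surgery and medication at around 2", in per cent). With a mean rate of 0.06 and two-sided 0.05:

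n = [1.960·√(2·0.06·0.94) + 0.842·√(0.10·0.90 + 0.02·0.98)]² / 0.08² = (0.658 + 0.279)² / 0.0064 ≈ 137.2, rounded up to 138 per arm, or 276 in total.

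Power at 138 per arm is 0.802. The stated size reproduces exactly. It uses its 0.05 once, on recurrence rates, so it does not identify a primary volume test.

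**Step 2: independent visits.** The chance of at least one p < 0.05 with no true difference is 1 − 0.95^k.
- k = 4: 1 − 0.8145 = 18.5%
- k = 5: 1 − 0.7738 = 22.6%

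**Step 3: correlated visits.** This was simulated with 1,000,000 draws of k standard normal test statistics, counting a draw if any |Z| > 1.96. Correlation was either equal between all visits or decaying as r^|i−j| (AR(1)).

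| r | 4 visits, equal | 4 visits, AR(1) | 5 visits, equal | 5 visits, AR(1) |
|---|---|---|---|---|
| 0.5 | 15.6% | 16.7% | 18.3% | 20.1% |
| 0.7 | 13.0% | 14.3% | 14.9% | 17.2% |
| 0.8 | 11.5% | 12.7% | 12.8% | 14.9% |
| 0.9 | 9.3% | 10.4% | 10.2% | 11.8% |

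Relative to 5%, the smallest value is 9.3/5 ≈ 1.9 and the largest, from Step 2, is 22.6/5 ≈ 4.5.

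**Step 4: the planned two-stage test itself.** Shapiro–Wilk followed by t-test or Mann–Whitney was simulated on lognormal volumes (log-SD 0.8, an assumption), with 138 per arm and 4,000 replicates. The last visit alone rejected in 4.4% to 5.6% of replicates. At least one of four visits rejected in 16.2% at latent correlation 0.5, 12.8% at 0.7 and 9.5% at 0.9. The excess therefore comes from the number of visits, not from the pre-test.

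**Step 5: which visits can show a treatment effect.** Intervention description {11a} allows tranexamic acid to start up to 48 h, and embolization up to 72 h, after surgery. These are upper limits, so some patients may already be treated at the day-1 scan, but many may not be. Four visits is the fairer count, although nothing in {20a} removes day 1 from testing.

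**The case against.** The strongest reply is that the article sets no rule that any significant visit counts as success. It also states no family-wise 5% that could be breached: the 0.05 in {20a} is per test, and a single visit does hold close to it. A rule requiring significance at every visit would keep the error at or below 5%. All of this is correct, so the size must be stated conditionally. The gap remains, because no decision rule of any kind is given.

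Four stronger readings are tempting, and the documents do not support them.
- A reader might infer that the error rate is about three times a stated 5%. Three times fits four visits at moderate correlation (equal correlation 0.4 to 0.7 gives 16.5% to 13.0%), but the correlation is unknown.
- A reader might blame the Shapiro–Wilk switch for extra error, or for a hypothesis that changes between visits. Step 4 shows no inflation at a single visit. For lognormal volumes at n = 138, the pre-test rejects in about 96% of samples at log-SD 0.3 and in practically all at 0.5 and above, so under that assumption switching would be rare. The argument for one fixed method is clarity.
- The plural in {20c}, "If a significant amount of data is missing for any of the primary endpoints", might look like evidence of several primary tests. That sentence concerns missing data and defines no test.
- The figures might be read as the chance of wrongly declaring equivalence. The Abstract and Trial design {8} do frame the trial as an equivalence question, but the figures concern falsely declaring a difference. The equivalence wording is a separate problem.

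**Conclusion.** The point stands in conditional form. Separate visit-by-visit tests at an unadjusted 0.05 are prescribed for the primary outcome, and no primary visit, contrast, testing order or adjustment is fixed. If significance at any visit is taken as a positive primary result, the chance of falsely declaring a difference is about 9% to 19% over the four visits after day 1, and about 10% to 23% over all five. Confidence is high in the textual gap. The exact multiple depends on the any-visit reading and on a correlation that the article does not report. The sample size arithmetic is not affected.

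**What to change.** Before outcomes are examined by arm, amend {20a} to name one primary between-arm contrast at 0.05, with one analysis method fixed in advance in place of the Shapiro–Wilk switch. Two choices would serve:
- the difference in volume at month 3; or
- one pre-specified treatment contrast from a single longitudinal model of the volumes after day 1, which is closer to the time-course wording of the Primary objective.

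Either choice restores 5% for the primary test. Splitting the level would also hold it to at most 5% (0.05/4 = 0.0125 per visit, or 0.05/5 = 0.01), but would leave several primary tests.

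Report the remaining visits as supportive estimates with confidence intervals and no significance claims. Do not count the day-1 scan as a test of treatment effect. Label within-arm tests as descriptive, since they do not compare treatments. State the chosen contrast consistently with the equivalence wording in the Abstract and Trial design {8}.

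The cost is a few sentences and no new data. The downside is that the other visits can no longer carry a confirmatory claim.
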